# Medicine in spine exercise (MiSpEx) for nonspecific low back pain patients: study protocol for a multicentre, single-blind randomized controlled trial

**DOI:** 10.1186/s13063-016-1645-1

**Published:** 2016-10-20

**Keywords:** Sensorimotor training, Motor control, Low back pain, Exercise, Functional capacity, Individualized intervention

## Abstract

**Background:**

Arising from the relevance of sensorimotor training in the therapy of nonspecific low back pain patients and from the value of individualized therapy, the present trial aims to test the feasibility and efficacy of individualized sensorimotor training interventions in patients suffering from nonspecific low back pain.

**Methods and study design:**

A multicentre, single-blind two-armed randomized controlled trial to evaluate the effects of a 12-week (3 weeks supervised centre-based and 9 weeks home-based) individualized sensorimotor exercise program is performed. The control group stays inactive during this period. Outcomes are pain, and pain-associated function as well as motor function in adults with nonspecific low back pain. Each participant is scheduled to five measurement dates: baseline (M1), following centre-based training (M2), following home-based training (M3) and at two follow-up time points 6 months (M4) and 12 months (M5) after M1. All investigations and the assessment of the primary and secondary outcomes are performed in a standardized order: questionnaires – clinical examination – biomechanics (motor function). Subsequent statistical procedures are executed after the examination of underlying assumptions for parametric or rather non-parametric testing.

**Discussion:**

The results and practical relevance of the study will be of clinical and practical relevance not only for researchers and policy makers but also for the general population suffering from nonspecific low back pain.

**Trial registration:**

Identification number DRKS00010129. German Clinical Trial registered on 3 March 2016.

**Electronic supplementary material:**

The online version of this article (doi:10.1186/s13063-016-1645-1) contains supplementary material, which is available to authorized users.

## Background

Nonspecific low back pain is the most common kind of musculoskeletal pain with a lifetime prevalence of up to 90 % [1, 2] and of particular relevance in industrialized countries. Point prevalence varies between 30 and 50 %, depending on age and sex [1]. When focusing on competitive elite athletes only, actual research findings estimate the lifetime prevalence at 60 % and the point prevalence at 18 % [3, 4]. Just as in the general public, prevalences vary in different subsamples of athletes, depending on the specific sport, age or sex [5, 6].

Neuromuscular and/or structural deficits [7, 8], mostly accompanied by psychological or social factors (‘yellow flags’) [9], are known risk factors for both the onset and chronification of nonspecific low back pain. With valuable impact on these factors and the back pain itself, target-oriented movement training is of increasing relevance in (secondary) prevention and therapy [10, 11]. Evidence-based therapeutic approaches have changed and are no longer solely passive-reactive but multidisciplinary-active with a major physical activity part. However, the evidence for the effectiveness of physical activity in the therapy of nonspecific low back pain is mixed. A recent meta-analysis indicates that physical activity has positive effects in the therapy of nonspecific low back pain [10]. In addition, the authors show that, using pooled subgroup effects, coordinative and stabilizing training also has an effect by addressing sensory deficiencies. The latest Cochrane review, however, only provides low to moderate quality evidence that isolated motor control exercises are able to improve pain in the short, intermediate or long term [11]. The authors conclude that a final proof for the efficacy of motor control exercise on relevant functional factors like kinematics, strength, postural control and pain is still missing.

A further potential explanation for the lack of consistent evidence for the beneficial impact of physical activity on nonspecific back pain may be that the impact of physical activity on pain is moderated by contextual and individual psychological and social factors (so-called yellow flags [12]). A better understanding of the role of these moderating factors is crucial to evaluate the role of physical activity for the treatment of chronic back pain and eventually enable the personalization of such physical activity interventions. Individualizing the sensorimotor therapy with respect to individual skill level, demands, preferences, and potential moderating factors such as pain, physical activity, pain experience, stress, life context and the medical care context may lead to greater therapy success [12]. Likewise, determining the optimal dose for treating patients as individuals is still a matter of debate [13, 14].

Against the background of the need for further evidence for the efficacy or non-efficacy of motor control exercise targeting neuromuscular factors like kinematics, strength, postural control and pain [11], the purpose of this study is to test (1) the feasibility and (2) the efficacy of individualized motor control interventions in nonspecific low back pain patients. We hypothesize that individualized motor control exercises lead to an improvement in motor function, assessed as maximal back extension torque, in low back pain patients and in comparison to a control group. Secondary research questions are: (1) does individualized motor control exercises lead to an improvement in motor function, pain and/or pain-related variables in low back pain patients and compared with a control group at short and/or long term and (2, exploratory) to what extent do moderating factors play a role in non-responder detection dose-response considerations and therapy individualization?

## Methods/Design

### Study design and flow

The study consists of a multicentre (Appendix A), single-blind two-armed randomized controlled trial to evaluate the effects of a 12-week individualized sensorimotor exercise program on pain, pain-related outcomes and function in nonspecific low back pain adults compared with a waiting control group. The study has been approved by the independent Ethics Committee of the University of Potsdam (committee’s reference number 3/2016; amendment for number 47/2013). Date of preliminary approval was the 25 January 2016; date of the final approval was the 9 May 2016. The study was planned and is performed in agreement with the Declaration of Helsinki (Version Fortaleza 2013). Trial registration number is DRKS00010129 (DRKS, German Clinical Trials Register, drks.de; 3 March 2016). All adverse events will be reported.

Primary outcome is trunk extension strength [Nm]. The assessment and analyses of all records are performed by blinded evaluators. Five assessment visits (M1-M5) will take place over a period of 12 months.

### Participants

#### Sample size determination

A pilot feasibility study was conducted (unpublished material). The therein found outcome with the largest effect size was selected as the primary outcome for the present study. Thus, primary outcome is maximal back extension torque. Sample size calculation was based on the effect size of d = 0.24 (based on the changes in primary outcome from baseline to post-intervention (12 weeks)). For the main study, effect size was conservatively completed to d = 0.2.

Participants are allocated to intervention or control group at the ratio of 2:1. Normal distribution and variance equality are assumed. Following a determined α-error probability of 2.5 % and a β-error probability of 0.1, a minimal sample size of 1186 patients are consequently to be included into analysis (*n* = 791 in the intervention and *n* = 395 in the control group). As a dropout rate of 30 % is assumed, a total of *N* = 1542 participants are included in the study. Although motor control and stabilizing exercise are likely to show equal effects for the general population and for top athletes [15], medical access and the potential to implement medical exercise regimes into everyday life differ between these populations (e.g. training schedule, competitions). According to study aim 1, and beside the studies’ main target group, we make additional effort to also recruit a sample of athletes to gain further (beyond the main analyses) insight and test the feasibility in this much less investigated population. For dichotomization purpose, only top competitive athletes (A to D pool, participating in top level international, federal or state competitions) are further treated as athletes.

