### Statistical analysis

Data is collected and analysed centrally after assessment completion. Following visual and physiological range plausibility control, a gain score analysis (change score analysis) using the mean difference between M1 and M3 for between-group differences of the primary outcome is performed.

Hypotheses testing for all other measurement times and secondary outcomes are performed using particular fitting regressional and variance analytical testing. Potential mediators and confounders like the amount of physical activity, psychosocial scores, age, gender, initial pain level and body weight will be analysed using multiple regression mediating analyses [35] or included into variance analyses as covariates. For mediation analyses, total as well as direct and indirect effects are calculated. Sobel testing and 95 % confidence interval (CI) bias corrected bootstrapping (n_sub-samples_ = 10,000) are conducted for indirect effect quantification [36–38].

All statistical procedures are executed after the examination of underlying assumptions for parametric or rather non-parametric hypotheses testing. Due to the explorative analyses of the secondary outcomes, no alpha-error adjustment is performed. To increase statistical power, missing values are multiple imputed using standardized procedures [39] and only following (in case of psychometric scores) specific test manuals. The one-sided a priori level of significance is set at α = 0.025 for all statistical analyses.

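### The 30 % dropout allowance is added to the analysed number (1186 × 1.3 = 1542) instead of divided out (1186 / 0.7 = 1695), so 30 % loss by M3 leaves about 1079 observed outcomes and about 87 % power, not 1186 and 90 %

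*Protocol article*

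**What the plan says.** Under Sample size determination, the protocol article sets the error rates: "Following a determined α-error probability of 2.5 % and a β-error probability of 0.1". The planning effect comes from a pilot value of 0.24, and the "effect size was conservatively completed to d = 0.2". On allocation and distribution it says "Participants are allocated to intervention or control group at the ratio of 2:1" and "Normal distribution and variance equality are assumed". From these inputs "a minimal sample size of 1186 patients are consequently to be included into analysis", split as 791 intervention and 395 control. The next sentence assumes a dropout rate of 30 % and gives the enrolment target: "a total of *N* = 1542 participants are included in the study".

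Two statements under Statistical analysis bear on this. The test is one-sided: "The one-sided a priori level of significance is set at α = 0.025 for all statistical analyses". The primary comparison is the between-group difference in change from M1 to M3, with missing values multiply imputed.

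**The concern.** A dropout rate is ordinarily the share of enrolled participants who are lost, and the article gives no other definition. To end with a required number after such a loss, that number is divided by one minus the rate. The stated target instead matches the required number plus 30 % of itself. This falls short because 30 % of the larger enrolled number is more than 30 % of the smaller analysed number.

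At stake is whether the stated 90 % power is true under the article's own assumptions. The 1186 is presented as a minimum, so a target that misses it under the assumed dropout contradicts the sentence just before it.

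**Working it through.** Inputs, all from Sample size determination except the sidedness, which is from Statistical analysis: alpha 0.025 one-sided, beta 0.1, d = 0.2, equal variances, 2:1 allocation, 1186 to be analysed, 30 % dropout, 1542 enrolled.

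1. **Reproduce the analysed number.** With 2:1 allocation the control group needs (1 + 1/2) × (z₀.₉₇₅ + z₀.₉₀)² / d² = 1.5 × (1.960 + 1.282)² / 0.04 = 394.03, rounded up to 395. That gives 790 intervention and 1185 in total. The t-test version gives 394.7, again 395. The power of the stated 791 + 395 by noncentral t is 90.0 %. The stated 1186 therefore reproduces. Other readings of alpha do not give it: two-sided 0.025 gives 1398 and one-sided 0.05 gives 966.

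2. **Reproduce the enrolled number.**
   - Adding the allowance: 1186 × 1.30 = 1541.8, rounded to 1542. This is the stated figure.
   - Dividing it out: 1186 / (1 − 0.30) = 1694.3, rounded up to 1695 (791 / 0.7 = 1130 and 395 / 0.7 = 564.3, so 1130 + 565). This is 153 more than 1542.

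3. **What 1542 leaves after 30 % loss.** 1542 × 0.70 = 1079.4, so about 1079 (about 720 against 360). The shortfall is 1186 − 1079 = 107, and 107 / 1186 = 9 %.

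4. **Power with 1079.** With arms of 2N/3 and N/3, the expected test statistic is d × √(2N/9). For N = 1079 this is 0.2 × √239.8 = 3.097. Power is Φ(3.097 − 1.960) = Φ(1.137) = 87.2 %. Noncentral t also gives 87.2 %. Beta is therefore 0.128.

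5. **Effect detectable at 90 % power with 1079.** (1.960 + 1.282) / √239.8 = 0.209, against the planned 0.200.

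6. **Dropout that 1542 can absorb.** 1 − 1186 / 1542 = 356 / 1542 = 23.1 %.

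**The case against.** Four arguments can be made for the stated figures.

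- **The consequence is small.** Power falls by just under 3 points and the detectable effect moves from 0.200 to 0.209. The planning effect was already reduced from the pilot's 0.24, and at 0.24 power with 1079 would be 96.0 %. This stands as a limit on the harm. It does not make the stated 90 % true, because the article plans on 0.2. The pilot value is also a weak cushion, because the primary outcome was chosen as the one with the largest pilot effect.
- **Multiple imputation may keep everyone in the analysis.** The correct description of the 1079 is therefore participants with observed M3 data, not participants analysed. The figures still do not reconcile. The dropout allowance is tied directly to the number to be analysed, so dropouts are counted as lost. Imputing a missing outcome does not in general restore the lost information. If it restored all of it, 1542 would give about 96 % power, which is not the stated figure either.
- **The timing of the 30 % is not given.** The primary comparison ends at M3 (12 weeks), while follow-up runs to M5 (12 months). If 30 % is the loss over the whole study, loss by M3 could be lower, and at 23.1 % or less 1542 would suffice. The article does not settle this. The sentence follows directly on the number to be analysed, which favours reading it as loss from the primary analysis.
- **The 30 % might be meant relative to completers.** The arithmetic would then be right, but the dropout rate among those enrolled would be 23 %, and the text would still need correcting.

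A reader might also infer that adjusting the primary analysis for baseline would recover the loss, so that more enrolment is unnecessary. The document does not support that, because it reports no M1–M3 correlation. Suppose d is standardised on the change-score SD and the M1 and M3 variances are equal. Adjustment then multiplies the variance by (1 + r)/2, and power with 1079 is 91.9 % at r = 0.7, 90.4 % at r = 0.8 and 88.8 % at r = 0.9. Whether 90 % is regained depends on an unknown value.

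**Conclusion.** The sample size sentence is wrong as written. The analysed number is correct for its inputs, and the error lies only in the dropout step. With 1542 enrolled and 30 % lost by M3, about 1079 have an observed outcome, 107 below the stated minimum, and power is about 87 % rather than 90 %.

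The 87 % is conditional on d = 0.2, on the 30 % applying by M3, on equal dropout in both arms, and on no information gain from imputation. A reader might take it as the trial's actual power, or conclude that the trial is seriously underpowered. The document supports neither: some of these conditions are not stated in it, and the shortfall under them is about 3 points. The test, its type I error and the quantity estimated are unaffected.

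**What to change.** Restate the sample size sentence in one of two ways:

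- 1542 enrolled with 30 % dropout by M3 gives about 1079 participants with an observed outcome and about 87 % power at d = 0.2; or
- 1542 enrolled supports 1186 analysed and 90 % power only if dropout by M3 is at most 23 %.

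Either version should say that the dropout rate is a share of those enrolled and that it refers to M3. If the 87 % is stated, name the assumptions of equal dropout and no gain from imputation beside it.

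The cost is one corrected sentence and a slightly less favourable power statement. The correction itself does not require a change in enrolment. If the sponsor wants to keep 90 % power and 30 % dropout together, the matching figure is 1695. Trial status reports 142 participants included at manuscript submission and none through the intervention, so at that stage the figures could be corrected before any primary outcome change was available.

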#### Recruitment, screening and informed consent

Representative volunteers are recruited at clinical low back pain consultation hours, through flyers, local newspapers and bulletins, and personal recruitment. Athletes are further recruited by personal approach in one of the participating study sites, mostly at the mandatory annual sports medical examination. Only general information is provided during recruitment. Interested persons are scheduled for a visit in one of the six study sites and then screened for eligibility. Males and females aged 18–65 years with chronic low back pain are considered eligible if they fulfil the following inclusion criteria: at least one episode (≥ 4 days) of nonspecific back pain in the last 12 months, ability to understand the extent and meaning of the study and to answer a questionnaire without help.

Exclusion criteria consist of acute infection, pregnancy, inability to execute a one-legged stance, diseases with contraindication for exercise (including spine complaints based on space-occupying, inflammatory, traumatic or systemic processes [12]) and change or progression in the severity, localization or type of back pain during the last 7 days. Following application of inclusion and exclusion criteria, patients are approved by the physician in charge. Each participant signs informed consent prior to study enrolment.

#### Randomization procedure and blinding

After inclusion and completing the first visit, volunteers are block-randomised (n_block_ = 18; 2:1 basis) into either the intervention or control group by the study coordinator. Randomization order follows the study inclusion order. Each study site receives its own randomization lists once a week from the primary study centre; the randomization sequence is generated using a computer-based algorithm (www.randomization.com). All assessors and study personnel other than the study coordinator (and the therapist) are blinded. Participants are told not to communicate their group allocation to other participants or study staff.

### Experimental procedure

In this multicentre intervention trial, a 12-week sensorimotor intervention is performed (3 weeks supervised centre-based followed by 9 weeks home-based) after the randomization (intervention group only). The control group does not receive any (additional) therapeutic or placebo treatment during this period. Each participant is scheduled for five measurement visits (M1-M5) prior to (M1) and following centre-based (M2), following home-based training (M3) and at two follow-up points in time (M4: 6 months after M1 and M5: 12 months after M1). All investigations and thus the assessment of the primary and secondary outcomes are performed in a standardised order: questionnaires – clinical examination – biomechanics. Whilst all biomechanical assessments (including the primary outcome) are assessed at each visit, the clinical examination and questionnaires are assessed in a sequenced order. The experimental procedure is shown in detail in Fig. 1 and Additional file 1. Although the measurement periodization is defined, an individual tolerance time of 7 days (M2, M3), 14 days (M4) and 30 days (M5) is set.

**Fig. 1 Fig1:**
[figure not shown]
Study time bar and flow charts. All participants are scheduled to five visits with standardized assessment procedures. Subjects are 2:1 randomized into sensorimotor training (SMT) and control (CON) group for centre-based (3 weeks) and home-based phase (9 weeks). *M1-M5* visit measurement number 1 to number 5. Questionnaires: *CPG* Chronic Pain Grade questionnaire, *FABQ-D* Fear-Avoidance Beliefs Questionnaire, *TICS* Trier Inventory for Chronic Stress, *HADS-D* Hospital Anxiety and Depression Scale, *BSSS* Berlin Social Support Scales, *IPAQ* International Physical Activity Questionnaire, *RQ-2* the Relationships Questionnaire 2, *AEQ-PPS* Avoidance Endurance Questionnaire, *SES* socioeconomic status, sleep, *GH* general health, *LE* life events, motor function: *F* force/strength/torque, *CoP* centre of pressure; static balance, *CMJ* counter movement, *ROM* range of motion/kinematic analyses, *CRT* Chair Rise Test, *TuG* Timed Up and Go Test

#### Questionnaires – assessment of back pain and moderating factors

At each measurement day (M1-M5) a psychometric assessment is performed to detect the moderating factors (‘yellow flags’) for the chronification of back pain. The test battery will be rotated (Fig. 1) and is partially based on subscales in order to reduce the burden for participants. Pain is assessed by the Chronic Pain Grade questionnaire (CPG) [16], which allows a differentiation in the subscales pain intensity (PI: 0 = “no pain” to 100 = “the worst pain imaginable”), and disability (DS: 0 = “no disability” to 100 = “I was incapable of doing anything”) in the past 3 months. Furthermore, participants can get classified into one of the four hierarchical pain and disability grades ranging from low pain/disability (grade I) to high pain/disability scores (grade IV) [17].

The five moderating factors were assessed using the following psychometric instruments: (1) physical activity: International Physical Activity Questionnaire (IPAQ) [18] and type of physical activity. (2) Pain experience: pain-related cognitions by the Fear-Avoidance Beliefs questionnaire (FABQ-D, [19]), avoidance‐endurance‐behaviour by the Avoidance-Endurance Questionnaire (AEQ; [20] and anxiety and depression by the Hospital Anxiety and Depression Score (HADS-D; [21]) ). (3) Stress: chronic stress by the Trier Inventory of Chronic Stress (TICS; [22]) and critical life events in the last 3 months. (4) Personal life context: social support by the Berlin Social Support Scales (BSSS; [23], individual attachment style by the Relationship Questionnaire 2 (RQ‐2; [24, 25]) as well as the socioeconomic status (CASMIN; [26] and lifestyle (alcohol, smoking, general health and sleeping status). (5) Medical care context: health services options (see also DSF, [27]) .

### Physical examination

The medical/physical examination has two aims: first, secondary outcome variables are assessed; second, contraindications for the following motor function assessment are screened.

At M1, M3 and M5, the complete medical assessment, according to the expert consensus standards of the German Association for Sports Medicine and Prevention [28] are performed by a trained sports medicine physician. This examination consists of (1) a complete medical anamnesis, (2) a training anamnesis, and (3) a general-internal and an orthopaedic examination. At M2 and M3, only a brief anamnesis to assess potential clinically relevant changes is conducted. In case of potential relevant changes, a complete medical assessment is performed at M2 and M3 as well.

